## Clinical trial flow chart

|                                                          | Visit 1
(admission) | Follow-up*        |                     |                     |
|----------------------------------------------------------|------------------------|-------------------|---------------------|---------------------|
|                                                          |                        | Visit 2
(1M)   | Visit 3
(6M)     | Visit 4
(12M)    |
|                                                          |                        | 4
Week
±1wk | 24
Week
±4wks | 48
Week
±4wks |
| Obtaining consent                                        | X          |                   |                     |                     |
| Inclusion/exclusion criteria                             | X                      |                   |                     |                     |
| Height and weight/vital signs                            | X                      |                   |                     |                     |
| Demographic information and risk factors/medical history | X          |                   |                     |                     |
| Medication history                                       | X                      |                   |                     |                     |
| Investigation of cardiovascular event                    | X                      | X                 | X                   | X                   |
| Coronary angiography                                     | X                      |                   |                     |                     |
| Lt. ventricular assist device insertion                  | X                      |                   |                     |                     |
| Complications related to the procedure       | X                      |                   |                     |                     |
| Echocardiography                                         | X                      |                   |                     |                     |
| General blood chemistry test                             | X          |                   | X       |                     |
| Lactate, ScVO 2                               | X          |                   |                     |                     |

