## 6.2. Background

Cardiogenic shock usually occurs as a fatal complication of acute myocardial infarction, cardiomyopathy, myocarditis, and rarely, sepsis. In particular, shock occurs in 5-8% of cases of ST-segment elevation myocardial infarction, and despite the development of various treatment techniques such as coronary intervention and coronary artery bypass grafting, a very high mortality rate of about 40% is still reported [1]. Shock is a term that encompasses all clinical situations in which cellular respiration is not properly carried out due to inadequate oxygen supply to tissues. It was first described by a French surgeon in 1737, and much progress has been made in the treatment and research of shock through the two World Wars and the Korean and Vietnam Wars. Types of shock include hypovolemic shock, represented by excessive bleeding due to trauma or surgery, septic shock caused by decreased peripheral vascular resistance due to infection, obstructive shock caused by circulatory disorders such as pulmonary embolism and cardiac tamponade, and cardiogenic shock caused by decreased cardiac output due to loss of cardiac pump function. The prominent characteristic of cardiogenic shock is that while the early mortality rate is the highest, once the patient recovers from shock, they can maintain a good quality of life with a better prognosis compared to other shocks. Currently, most of the studies related to cardiogenic shock published in Korea have selected patients through the arbitrary criterion of Killip class IV in acute myocardial infarction registry, so it is difficult to accurately determine the frequency and treatment status, mortality rate, etc. of cardiogenic shock caused by causes other than myocardial infarction. Since the adequacy of appropriate early treatment within 24 hours after the occurrence of cardiogenic shock determines the prognosis, it is essential to evaluate the treatment status and appropriateness of cardiogenic shock in Korea through research at the present time. In addition, the initial treatment of cardiogenic shock is primarily fluid therapy, mechanical ventilation, and vasopressor therapy, but if these are ineffective, left ventricular assist devices such as intra-aortic balloon pumps (IABP) and extracorporeal membrane oxygenation (ECMO) can be used. However, there are still no large-scale systematic studies in Korea to determine their effects.

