## **11. Clinical trial method**

### **11.1. Overview**

Shock patients with cardiogenic shock caused by acute myocardial infarction, myocardial disease, myocarditis, etc. will be registered both retrospectively and prospectively for two and a half years before and after IRB approval. Patients undergoing coronary intervention and treatment are performed according to the standard method recommended by the Korean Society of Cardiology. If the patient satisfies the above conditions and meets other inclusion and exclusion criteria, we obtain the patient's consent and enroll them in the study. On the day of shock occurrence, we perform physical measurements, blood tests, investigate the medication being taken, and record the most severe signs of vitality on that day. The maximum dose of medication used for shock treatment, the insertion of a left ventricular assist device, and indicators of shock deterioration and improvement are followed up. We conduct tests scheduled for the day of shock occurrence and one month, six months, and twelve months afterward to confirm whether a death event occurred. If the subject is unable to visit the hospital due to unavoidable circumstances, the trial responsible person or the person delegated by the trial responsible person may follow-up and check the subject's survival status and death event by phone.

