## 12. Observation items/clinical examination items and observation/testing methods

### 12.1. Visit 1 (day of shock occurrence)

#### ① Written informed consent for patients enrolled

According to the scope of data collection, it is divided into prospective data collection subjects and retrospective data collection subjects.

- Prospective data collection subjects: The day of shock occurrence is after the IRB approval date
- Retrospective data collection subjects: The day of shock occurrence is before the IRB approval date

For prospective data collection subjects, before entering the clinical trial, the purpose and content of the trial should be explained in detail to the subject or legal guardian (in the case of a subject who cannot provide consent for the trial), and the written consent form should accurately record the signature dates of the subject and investigator. The original signed consent form is kept by the subject, and a copy is provided to the subject. If the subject is unable to consent on the day of the shock occurrence, the consent form is obtained from the representative of the accompanying subject. In this case, the principal investigator and sub-investigator must inform the subject or the subject's representative about the clinical trial as soon as possible and obtain consent to continue participating in the trial. If the subject recovers to a condition where consent can be given, the consent form is obtained from the subject.

For retrospective data collection subjects, only data corresponding to the study protocol are collected until IRB approval is obtained without written consent. However, among shock occurrence subjects before IRB approval, those who have obtained written consent are eligible for both prospective and retrospective data collection.

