#### ④ Physical measurements and vital signs

Height and weight are measured. Vital signs including blood pressure, and heart rate are measured before any other planned tests are conducted.

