## **15. Evaluation criteria for effectiveness, and evaluation and interpretation methods (statistical analysis)**

### **15.1. Primary Endpoint**

In-hospital death

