### **15.3. Statistical analysis**

We aim to identify predictors of in-hospital death in patients who experience shock using binary logistic regression analysis. This type of analysis requires 10-15 events per independent variable, and with an expected mortality rate of about 40%, or approximately 400 deaths, we have sufficient events to study various risk factors. The goodness-of-fit of the model will be assessed using the C-statistic and Hosmer-Lemeshow test. In addition, we plan to compare the in-hospital death rate between patients with and without left ventricular assist devices using chi-square tests among those who receive a certain level of vasoactive drugs. We also aim to identify predictors of successful removal of the ECMO device and procedure-related complications such as bleeding, thrombosis, and limb ischemia using binary logistic regression analysis in patients who undergo ECMO. Finally, we plan to evaluate overall death over five years using Cox survival

analysis. We will assess the goodness-of-fit of the model by checking Schoenfeld's residuals and identify the hazard of each risk factor.

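### The device comparison in section 15.3 has no time anchor: deaths before an intended insertion count as no-device deaths, and the drug-level restriction is not limited to values before insertion

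*Protocol*

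**What the plan says.** The primary endpoint is "In-hospital death" (protocol, section 15.1). Section 15.3 plans to compare it "between patients with and without left ventricular assist devices using chi-square tests among those who receive a certain level of vasoactive drugs". Section 9.3 defines the two groups by insertion or non-insertion, with targets of more than 400 and more than 600 patients. No insertion window, landmark or time-dependent definition of device exposure appears.

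On timing, section 11.2 has a device typically inserted once drug treatment has failed, with earlier use left to the operator in exceptional cases. Section 6.2 says of cardiogenic shock that "while the early mortality rate is the highest".

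On the drug level, section 15.3 gives neither the threshold nor the time at which it is measured. The only drug amount the protocol says is recorded is in section 11.1, which lists for follow-up "The maximum dose of medication used for shock treatment, the insertion of a left ventricular assist device" and indicators of worsening and improvement.

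Section 9.3 concedes that the groups are not comparable on equal terms because most device patients are critically ill. It says nothing about the timing of insertion relative to death.

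**The concern.** To enter the device group a patient must survive from shock onset to insertion. To enter the no-device group a patient need not survive at all. Someone for whom a device was intended, but who dies first, leaves the device group and becomes a death in the other. A device with no effect then looks protective.

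The severity caveat in section 9.3 does not cover this. Severity confounding works against the device and immortal time works for it. A crude chi-square test mixes the two in unknown proportions.

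The restriction adds a second problem. If the level is read from a maximum dose with no time limit, that maximum may occur after insertion and may have been altered by the device. Who enters the comparison can then depend on a consequence of the exposure.

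Estimating the treatment effect of IABP and ECMO is a stated purpose (section 6.1), and section 9.3 powers this comparison. If insertion times are not captured, no later analysis can separate the components.

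**Working it through.** **1. The plan's own figure.** Inputs from section 9.3: 400 and 600 patients, death rates 0.3 and 0.4. Alpha is not stated; two-sided 0.05 is assumed. The odds ratio is (0.4/0.6)/(0.3/0.7) = 1.556. With the Fleiss-Tytun-Ury correction and r = 1.5, n' = 400 − 2.5/(1.5 × 0.1) = 383.3. Then

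z = (0.1 × √383.3 − 1.96 × √(1.667 × 0.36 × 0.64)) / √(0.21 + 0.24/1.5) = (1.958 − 1.215)/0.608 = 1.22,

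which gives power of 88.9% (stated: about 88%). For 360 and 540 patients it is 85.3% (stated: 84%). The power arithmetic is not at issue.

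**2. Moving deaths, using protocol figures only.** Suppose the device does nothing and mortality is 40% (section 15.3) in both groups: 400 intended for a device with 160 deaths, 600 not intended with 240 deaths. If k intended patients die before insertion, the observed rates are (160 − k)/(400 − k) and (240 + k)/(600 + k). The odds ratio, no device to device, is [(240 + k)/360] / [(160 − k)/240].

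| k | Device | No device | Odds ratio |
|---|---|---|---|
| 10 | 150/390 = 38.5% | 250/610 = 41.0% | 1.11 |
| 20 | 140/380 = 36.8% | 260/620 = 41.9% | 1.24 |
| 30 | 130/370 = 35.1% | 270/630 = 42.9% | 1.38 |
| 40 | 120/360 = 33.3% | 280/640 = 43.8% | 1.56 |

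Forty misplaced deaths, 10% of the 400 expected, reproduce the design odds ratio with no device effect.

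**3. How many deaths might be misplaced?** This depends on timing, which the protocol does not give. Assumptions: mortality 36% whatever the group (0.4 × 0.3 + 0.6 × 0.4), 45% intended for a device, a share e of deaths spread evenly over the first 24 h, later deaths all after insertion, and exponential time to insertion with mean m hours. The share of intended-device deaths that are misplaced is

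q = e × (m/24) × (1 − exp(−24/m)).

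Device mortality is 0.36(1 − q)/[0.36(1 − q) + 0.64]. No-device mortality is (0.198 + 0.162q)/(0.55 + 0.162q).

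| e | m (h) | q | Device | No device | Gap (points) |
|---|---|---|---|---|---|
| 10% | 2 | 0.008 | 35.8% | 36.2% | 0.35 |
| 30% | 2 | 0.025 | 35.4% | 36.5% | 1.05 |
| 30% | 6 | 0.074 | 34.3% | 37.4% | 3.10 |
| 30% | 12 | 0.130 | 32.9% | 38.4% | 5.49 |
| 45% | 24 | 0.284 | 28.7% | 41.0% | 12.25 |

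Gaps are from unrounded rates. If later deaths are instead spread over days 2 to 14, some of them also precede insertion. In the last row q becomes 0.2845 + 0.55 × (24/312) × exp(−1) = 0.300 and the gap 12.95.

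**4. Effect on the test.** With 400 and 600 patients, the rejection probability is about Φ((gap − 1.96 × s₀)/s₁), where s₀ and s₁ are the pooled and unpooled standard errors, both about 0.031. A gap of 3.10 points gives (0.0310 − 0.0608)/0.0309 = −0.96, or about 17%. A gap of 5.49 points gives (0.0549 − 0.0608)/0.0308 = −0.19, or about 42%. The nominal level is 5%.

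None of these figures applies the drug-level restriction, which cannot be modelled because it is undefined.

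**The case against.** The strongest objection is that the bias may be small. Section 15.3 compares only patients who reached a given drug level, so some of the earliest deaths leave both groups. Section 9.1 includes shock during coronary intervention and section 11.2 allows more aggressive insertion, and both can shorten the delay. If 40% of devices went in at once and the rest at a mean of 6 h, with 30% of deaths early, q would fall to 0.6 × 0.074 = 0.044 and the gap to just under 2 points. This stands: the size is unknown, and the figures above are not predictions.

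It can also be said that this is an observational registry, that the comparison is secondary to the prognostic model, and that a statistical analysis plan could define the drug level. The last point is fair for the threshold. It does not reach the with/without comparison, which the protocol itself fixes.

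Three stronger readings go beyond the text:

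- That all early deaths fall in the no-device group. Only deaths before an intended insertion are misplaced.
- That the analysis is conditioned on post-insertion severity. Section 11.1 also asks sites to "record the most severe signs of vitality on that day", but that describes data collection. Nothing says that those values enter the chi-square test, or that the drug level is the maximum dose. What can be said is that nothing prevents it.
- That time zero is contradictory. The flow chart labels Visit 1 as admission, but sections 11.3, 12.1 and 12.2 all anchor to the shock event. The label and the different vital-signs wording in section 12.1 are minor points to tidy and add nothing to the bias argument.

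**Conclusion.** The point holds in limited form. Followed as written, section 15.3 counts deaths before an intended insertion as no-device deaths, a bias towards the device that the caveat in section 9.3 does not cover. The restriction on drug level can also take in values from after insertion.

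A reader might infer that the plan will show devices to be protective. The documents do not support that: severity confounding runs the other way, and the net direction cannot be determined. The effect of a restriction on post-insertion values has not been quantified.

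On size, the table of moved deaths rests only on protocol figures and the assumption of no device effect. The range of under 1 to about 12-13 points rests on assumed timings (10-45% of deaths within 24 h, mean 2-24 h to insertion) and ignores the drug-level restriction. The bias may be negligible or as large as the planned effect, and the plan as written offers no way to tell which.

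**What to change.** In section 15.3:

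- State shock onset as time zero.
- Replace the crude comparison of in-hospital death with a landmark analysis: patients alive and in hospital at a fixed, prespecified hour after onset, classified by device status at that hour. Risk-set matching on time since onset is an alternative.
- If device enters the Cox model, which the section does not say, enter it as time-dependent from insertion.
- Define the drug-level restriction and any severity covariates from values before insertion, or at the landmark or matched time for patients without a device.

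Record insertion time and the pre-insertion drug dose on the e-CRF where the chart has them. Lactate is already scheduled by time from onset (flow chart, footnote 5).

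The cost is two or so data fields and modest analysis work. Patients who die before the landmark leave that comparison, devices inserted after it count as no device, and some retrospective records may lack exact times. The change removes the timing bias; it does not remove severity confounding, so the caveat in section 9.3 should stay.

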## **10. Duration of clinical trial**

IRB approval date ~ December 31, 2019 (registration period: IRB approval date ~ December 31, 2018).

Data collection period: January 1, 2014 ~ December 31, 2019 (6 years).

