### 11.3. Follow-up schedule

Clinical follow-up: date of shock occurrence, 1, 6, 12M

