## ⑦ Survival and death event investigation

## ⑧ Echocardiography

## ⑨ Coronary angiography for ischemic heart disease

## ⑩ Insertion of left ventricular assist device and investigation of complications

**12.2. Follow-up**

Visits are conducted at 1 month, 6 months, and 12 months after the shock event for the following tests and procedures. Information gathering through phone (landline contact) is also allowed without the subject's visit.

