## **18. Criteria for the medical treatment of subjects after the clinical trial**

After the 12-month study is completed, participants will continue to periodically visit the outpatient clinic according to each treatment provider's follow-up criteria to receive physical examinations and evaluations. They will also receive ongoing education to seek immediate consultation in case of symptoms such as chest pain, heart failure, or arrhythmia. In the event of adverse reactions or the need for hospitalization, the researchers will make every effort to minimize the risk.

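### The Cox analysis of death is set over five years, but scheduled follow-up ends at 12 months and no source of later deaths is named

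*Protocol*

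**What the plan says.** Section 15.3 (Statistical analysis) sets the horizon of the protocol's only time-to-event analysis: "Finally, we plan to evaluate overall death over five years using Cox survival" analysis, with a check of Schoenfeld residuals and an estimate of the hazard for each risk factor.

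The operational sections describe a shorter study:

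- Section 11.3: "Clinical follow-up: date of shock occurrence, 1, 6, 12M".
- Section 12.2: "Visits are conducted at 1 month, 6 months, and 12 months after the shock event for the following tests and procedures". Telephone contact may replace these visits; no later contact is listed.
- Flow chart: the last column is Visit 4 (12M), timed at week 48 with a window of 4 weeks either side.
- Section 18: "After the 12-month study is completed, participants will continue to periodically visit the outpatient clinic", under each provider's own follow-up criteria.
- Section 10: "registration period: IRB approval date ~ December 31, 2018", and "Data collection period: January 1, 2014 ~ December 31, 2019 (6 years").
- Section 11.1: patients are "registered both retrospectively and prospectively for two and a half years before and after IRB approval".
- Section 12.1, item ① (consent), on retrospective subjects: "only data corresponding to the study protocol are collected until IRB approval is obtained without written consent".

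Secondary endpoint 2 in section 15.2 is death during follow-up, with no time limit given.

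**The concern.** The analysis section names a horizon five times as long as the follow-up that the rest of the protocol provides. No section mentions death-registry linkage, later telephone contact or any other way to learn of deaths after month 12.

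Any information after month 12 would therefore be unscheduled. It would come mainly from the earliest calendar years, and possibly from selected subjects, because a retrospective subject can give written consent personally only if still alive. If the sentence stays, the analyst must either choose a horizon once the data are in, or report a five-year result that rests on a small and perhaps unrepresentative part of the cohort.

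**Working it through.** **1. The plan's own figures.** The protocol gives no event count, power or precision for the Cox analysis. Two related figures can be checked.

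- *Accrual (section 9.3).* 1,800 infarctions per year × 5.5% = 99, which the protocol rounds to about 100. Adding at least 100 from other causes gives about 200 per year, and 200 × 5 years = 1,000. This reproduces. The five years here are the registration span, not the time each subject is observed.
- *Power for in-hospital death (section 9.3).* With 400 against 600 subjects, 0.3 against 0.4, a continuity correction and two-sided alpha 0.05 (assumed; the protocol states none), power is 88.9% against the stated 88% or so. With 360 against 540 it is 85.3% against the stated 84%. These agree to within about a point, and nothing below touches them.

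**2. Follow-up by schedule.** The last contact is at week 48 ± 4, that is week 44 to week 52, or 44 × 7 = 308 to 52 × 7 = 364 days after shock. Share of subjects followed to five years by scheduled contacts: 0%.

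**3. Follow-up by calendar, if data were gathered on everyone up to the cut-off.** For a shock on date *t*, potential follow-up = 31 December 2019 − *t*.

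- Earliest onset, 1 January 2014: 6.0 years.
- Latest onset, 31 December 2018: 1.0 year.
- Mean under uniform accrual: (6.0 + 1.0) / 2 = 3.5 years.
- Five years or more requires onset by 31 December 2014. Under uniform accrual that is 365 of 1,826 days = 20.0%, or about 200 of 1,000. The other 80% or so cannot reach five years.
- The accrual pattern is not stated. If 2014 supplied 10% to 40% of the cohort, 100 to 400 subjects could reach five years and 60% to 90% could not.
- With the expected in-hospital mortality of about 40% (section 15.3), the 200 become 200 × 0.6 = 120 alive at discharge (60 to 240 over the same range). That is a ceiling on the number at risk at five years, before any later death or loss to follow-up.

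**4. Who the 2014 subjects are.** The protocol gives no approval date. Two and a half years from 1 January 2014 is about 1 July 2016, and a further two and a half years ends in December 2018, which matches the close of registration. On that inferred date all 2014 onsets are retrospective. If section 12.1 means that data without consent stop at IRB approval, such a subject has at most about 2.5 years of data (1 January 2014 to mid-2016).

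**5. Does 12 months work for everyone?** Not without a further rule. On the same reading of section 12.1, a non-consenting subject whose shock fell in the year before approval has less than 12 months of data. Under uniform accrual that year holds 1/5 of 1,000 = 200 subjects, which is the upper limit, reached only if none of them consented. A Visit 4 contact at week 44 also falls short of 12 months. A 12-month analysis therefore still needs censoring at the last point of observation.

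**The case against.** **Five years may mean the study period.** Section 9.3 uses a five-year period for registration, and section 11.1 gives two and a half years either side of approval. The sentence could simply mean deaths recorded during the study. This is a fair reading, and section 15.3 does not literally promise a five-year survival estimate. But the sentence then gives no horizon per subject and still does not match the 12-month schedule, so it needs correction on either reading.

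**Cox regression does not need every subject to reach the horizon.** This stands. Staggered entry and administrative censoring are handled, and hazard ratios for risk factors can be estimated. A reader might infer that the hazard ratios would be biased. The documents do not show that: informative observation is plausible for subjects who consented after surviving, but neither its size nor its direction can be derived from the protocol.

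**Records may yield later deaths.** Inclusion criterion 5 covers consent to medical records throughout the study, and collection runs to 31 December 2019. So it would be wrong to infer that a 12-month cut-off costs no data. Some later deaths may be found in records, although no section plans for this.

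**Censoring rules belong in a statistical analysis plan.** Largely true, and their absence here is not the point. The point is that a horizon stated in the protocol conflicts with the protocol's own schedule and dates.

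**Conclusion.** The point holds in a limited form. Section 15.3 states a five-year horizon that sections 10, 11.3, 12.2 and 18 do not deliver. On the schedule no subject is followed to five years. By calendar only 2014 onsets could be: about 20% of the cohort under uniform accrual, 10% to 40% over the range shown.

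The conflict itself follows from the stated schedule and dates and needs no assumption. The percentages depend on the accrual pattern. The 2.5-year limit depends on an inferred approval date and on one reading of an awkwardly worded consent sentence.

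A reader might infer that the study's main result is at risk. It is not: the primary endpoint is in-hospital death, and the logistic model, the device comparison and the power statement are untouched. This is a secondary analysis whose wording should be fixed, not a fault that invalidates the design.

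**What to change.** In section 15.3, replace the five-year horizon with death within 12 months of shock onset. Censor each surviving subject at the earliest of 12 months, last contact and, for retrospective subjects without consent, IRB approval, if section 12.1 does limit their data in that way (the sponsor should clarify that sentence). Give secondary endpoint 2 in section 15.2 the same horizon.

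This is a change of wording. Its cost is that deaths recorded after month 12 leave this analysis. They can be reported in a supplementary analysis censored at last contact, without a five-year claim.

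If a longer horizon is truly intended, the protocol must instead name the source of survival data after month 12 and set a data cut-off that supports the chosen horizon. That costs more, because it means added follow-up or linkage and, for five years in subjects registered up to December 2018, a cut-off at the end of 2023 and not 2019.
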